#### Psychotherapy program

Cognitive Behavioural Therapy is widely recommended as a gold-standard psychological intervention for multiple mental health presentations [4, 62, 63], and has demonstrated effectiveness when delivered in groups (e.g., [64, 65]) and via telehealth (e.g., [66, 67]).

The psychotherapy program is a transdiagnostic CBT group adapted from the manualised Mood Management Course that was developed by the Centre for Clinical Interventions (CCI) [68]. The psychotherapy program also incorporates mindfulness practices, with a growing body of research suggesting that the integration of mindfulness and CBT can improve clinical outcomes [69, 70].

CBT proposes that the cognitive and behavioural factors which maintain mental health distress are amenable to change through recognising and challenging these unhelpful patterns [71]. As such, the psychotherapy group aims to develop skills in self-awareness, identifying and managing unhelpful thoughts and behaviours, and learning and practicing self-management strategies. Each session includes guided mindfulness practice. Each group is facilitated by a clinical or registered psychologist and a provisional psychologist.

To ensure parity with the CALM ‘lifestyle’ program, participants are sent a self-soothe hamper at commencement of the program, which includes items such as a colouring book, head massager, and stress ball. Participants are also encouraged to utilise mental health apps, to increase their engagement with skills such as mindfulness, breathing, thought logs, and cognitive disputation.

#### Randomization and blinding

Upon enrolment, participants are assigned a unique study identification (ID) number for randomisation purposes. After baseline assessment is complete, participants are assigned randomly to either the CALM group or the psychotherapy group. Allocation to the intervention arm is conducted using computer-generated block randomisation in a 1:1 ratio (CALM to psychotherapy). The allocation sequence is generated by an independent statistician. As randomisation occurs only when there are sufficient participants to form groups (minimum *n* = 5 per group), block randomisation is not feasible. Rather, a simple random allocation method is used within groups of participants which are ready to be randomised.

The Study Coordinator (unblinded) provides each participant with the schedule (for the group to which they have been allocated) and the technical support information (e.g., Zoom download, set up).

### Sample size

To assure non-inferiority hypothesis on the primary outcome, the maximum allowed upper limit of the 95% CIs (one-sided alpha of 5% was used for non-inferiority margin) of between-group mean difference on the PHQ-9 will be no larger than 2. This was based both on statistical reasoning (sample size and recruitment feasibility over the funded 18-month study period), clinical judgement and other psychotherapy trials using non-inferiority designs [72]. Assuming a standard deviation of 4, one-sided type I error = 0.025 and 80% power, a total sample size of *N* = 160 (*n* = 80 participants assigned to each group) will be required and inflated by 15% (*N* = 184) to allow for comparable attrition to that observed in our other telehealth trials (e.g., [18]).

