## Methods

### Study design

This is a two-arm, parallel-group, individually randomised group treatment (IRGT), non-inferiority trial. This single-site study is currently recruiting *N* = 184 participants from the Barwon and surrounding regions (Victoria, Australia). Participants are individually randomised (1:1 allocation) to either of the two group-based programs, both delivered via telehealth. All participants complete assessments prior to randomisation (baseline) and at program completion (8 weeks). Recruitment and program delivery are anticipated to occur over 50 weeks, from May 2021 to April 2022.

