Due to the individually randomised group treatment design, baseline assessment of eligible participants are ‘batched’ to ensure 50/50 randomisation to each arm whilst reducing the amount of time between baseline assessments and commencement of the program to which they have been assigned. In other words, baseline assessments are booked only once an adequate number of participants have enrolled to form groups (minimum 5, maximum 10, per group). At this point, participants are asked whether they have had any changes to medications or medical events since enrolment. If the time from enrolment to time of baseline assessments exceeds 2 weeks, they are re-assessed on the DQ5 to re-confirm eligibility.

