### Data analyses

To compare continuous outcomes on the PHQ-9 in the primary analysis, between-group mean difference and confidence intervals (CIs) will be estimated using generalised estimating equation techniques, with Huber Sandwich Estimator of variance to account for clustering [31, 73]. One-sided type I error of 0.025 will be used for all non-inferiority analyses. Effect sizes will be calculated using Cohen’s d. Exploratory analyses non-equivalence comparisons will examine remission (post-treatment score < optimal cut-score for a probable diagnosis of depression on PHQ-9 in participants who initially scored above Threshold) and recovery rate (reduction of at least 50% of pre-treatment PHQ-9 scores) rates. Two-sided alpha of 5% will be used. Reliable improvement is defined as a reduction of > 5 points on PHQ-9 scores based on severity classifications pre-to-post treatment.

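### N = 160 does not follow from the stated inputs, which give 126, and with no ICC or design effect reported the 80% power cannot be verified for this group-treatment design

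*Protocol article*

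**What the plan says.** All references are to the protocol article.

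- **Study design** describes a two-arm "individually randomised group treatment (IRGT), non-inferiority trial". Allocation is individual and 1:1.
- **Recruitment and informed consent** says that baseline assessments are booked only once "an adequate number of participants have enrolled to form groups (minimum 5, maximum 10, per group".
- **Sample size** sets the non-inferiority criterion: the upper confidence limit "of between-group mean difference on the PHQ-9 will be no larger than 2". It then gives the inputs and the requirement, "Assuming a standard deviation of 4, one-sided type I error = 0.025 and 80% power, a total sample size of" 160 participants (80 per arm), raised by 15% to 184 for attrition. The same paragraph says in parentheses that a "one-sided alpha of 5% was used for non-inferiority margin".
- **Data analyses** specifies generalised estimating equations "with Huber Sandwich Estimator of variance to account for clustering", and a one-sided type I error of 0.025 for all non-inferiority analyses.

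The Sample size section does not mention an ICC, a group size, a design effect or a non-zero true difference.

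**The concern.** The section lists inputs and an output, and the output does not follow from the inputs. The gap is about 27%, too large for rounding, and attrition does not explain it because the 15% is added after 160 is reached.

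The design also makes the missing quantity an important one. Participants treated in the same group may have correlated outcomes, and the article accepts this both in naming the design and in choosing the variance estimator. Power then depends on the ICC and the group size, and neither appears beside the power claim. A reader cannot tell whether 160 already allows for clustering, or how much clustering it can tolerate before power falls below 80%.

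**Working it through.** **Inputs.** From Sample size: margin 2, SD 4, one-sided alpha 0.025, power 80%, 80 per arm. From Recruitment and informed consent: groups of 5 to 10. Assumed here, because not stated: true difference 0, ICC from 0 to 0.10, equal group sizes.

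**Step 1: attempt to reproduce 80 per arm.**

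n per arm = 2 × (z₀.₉₇₅ + z₀.₈₀)² × SD² / margin² = 2 × (1.960 + 0.842)² × 16 / 4 = 62.8, so 63 per arm and N = 126. The exact t calculation gives 64 per arm and N = 128. The stated 160 is not reproduced.

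**Step 2: other standard settings, same margin and SD (n per arm).**

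| One-sided alpha | 80% power | 85% power | 90% power |
|---|---|---|---|
| 0.025 | 63 | 72 | 85 |
| 0.05 | 50 | 58 | 69 |

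None gives 80. The 5% alpha mentioned in the same paragraph widens the gap.

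**Step 3: power at 80 per arm if participants are independent.**

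SE = 4 × √(2/80) = 0.6325. Power = Φ(2/0.6325 − 1.960) = Φ(1.202) = 88.5%.

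**Step 4: what could bridge 63 to 80.** The ratio is 80/63 = 1.27. Several unreported inputs would produce it:

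- A design effect 1 + (m − 1) × ICC with m = 10 and ICC 0.03: 1 + 9 × 0.03 = 1.27, and 62.79 × 1.27 = 79.7, so 80 per arm.
- An SD of about 4.5: 2 × 7.849 × 4.5² / 4 = 79.5, so 80 per arm.
- A true difference of about 0.23 against CALM: 2 × 7.849 × 16 / (2 − 0.23)² = 80.2.
- A 20% loss allowance on the t-based figure: 64 / 0.8 = 80.

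The article does not show which of these, if any, was used.

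**Step 5: power at N = 160 with clustering.** SE = 0.6325 × √(1 + (m − 1) × ICC), where m is the number of evaluable members per group. The first figure in each cell uses the normal reference. The second uses a t reference with (number of groups − 2) degrees of freedom, that is 160/m − 2 = 30, 19.3 and 14. The article does not specify that reference.

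| Assumed ICC | m = 5 | m = 7.5 | m = 10 |
|---|---|---|---|
| 0 | 88.5% / 86.4% | 88.5% / 85.1% | 88.5% / 83.6% |
| 0.01 | 87.3% / 85.1% | 86.5% / 82.9% | 85.7% / 80.4% |
| 0.03 | 84.8% / 82.4% | 82.5% / 78.4% | 80.1% / 74.2% |
| 0.05 | 82.3% / 79.8% | 78.4% / 74.2% | 74.7% / 68.6% |
| 0.10 | 76.2% / 73.4% | 69.2% / 64.7% | 63.1% / 57.0% |

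With the normal reference, power falls below 80% once the ICC exceeds about 0.03 (m = 10), 0.04 (m = 7.5) or 0.07 (m = 5).

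**The case against.** The strongest reply is that the authors probably did allow for clustering and that the condensed article left the factor out. An ICC of 0.03 at the protocol's largest group size gives exactly 80 per arm and 80% power, and the article names the group-treatment design and a cluster-robust variance. This reply stands in part. A reader might infer from the silence that no ICC entered the calculation, or that 80% is not the power of this trial. The article supports neither: it shows only that no ICC is reported. Equally, it does not show that a design effect was used, since three other inputs reach the same total.

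A second reply is that the listed inputs need fewer participants than planned, so the error is on the safe side. That holds under independence, but not at moderate ICCs.

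A third is that the lower figures in the table depend on choices made here. That is fair. The ICCs are assumed, and the t reference is an assumption too: with groups of 7.5 or 10 at ICC 0.03 it is that reference which takes power below 80%. Ten is the maximum group size, so m = 10 is the upper end. The article does not say whether SD 4 is raw or residual, and adjustment for baseline PHQ-9 could raise power.

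That an article condenses a fuller protocol can excuse an omitted ICC. It does not excuse a stated total that the stated inputs do not give.

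**Conclusion.** The point holds as a certain arithmetic discrepancy together with a power claim that cannot be checked. The listed inputs give 126 (128 by t), not 160. At 160 they give 88.5% power if participants are independent and the true difference is 0. For the design as described, power at 160 runs from 88.5% (ICC 0) through about 80% (ICC 0.03, groups of 10) to 63% (ICC 0.10, groups of 10) by the normal approximation, and lower with few degrees of freedom. Which of these applies depends on a number that the article does not give.

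This does not show that the trial is underpowered. A reader might also infer that a failure to show non-inferiority would be uninterpretable. That does not follow: the result will be read from the confidence interval against the margin of 2, the planned interval allows for clustering, and neither the estimate nor the type I error depends on the planning ICC.

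**What to change.** Rewrite the Sample size paragraph as follows:

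1. State that margin 2, SD 4, one-sided 0.025, 80% power and true difference 0 give 63 per arm.
2. State the input actually used to go from 63 to 80 per arm: a design effect with its ICC and group size, or a different SD, true difference or loss allowance. If the record does not show it, say so; an ICC should not be chosen afterwards because it returns 80.
3. Reconcile the two one-sided alphas in the paragraph. Data analyses uses 0.025, which is also the level that matches the upper limit of a two-sided 95% interval.
4. Replace the bare 80% with power at the planned evaluable number over a stated ICC range, for example 0 to 0.10, naming the group size and the reference distribution. After 15% loss from 184 the evaluable number is 184 × 0.85 = 156, or about 78 per arm, slightly below 80.

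The cost is one paragraph. Enrolment, design and analysis need not change. The stated power may become less favourable.

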### Data analyses

To compare continuous outcomes on the PHQ-9 in the primary analysis, between-group mean difference and confidence intervals (CIs) will be estimated using generalised estimating equation techniques, with Huber Sandwich Estimator of variance to account for clustering [31, 73]. One-sided type I error of 0.025 will be used for all non-inferiority analyses. Effect sizes will be calculated using Cohen’s d. Exploratory analyses non-equivalence comparisons will examine remission (post-treatment score < optimal cut-score for a probable diagnosis of depression on PHQ-9 in participants who initially scored above Threshold) and recovery rate (reduction of at least 50% of pre-treatment PHQ-9 scores) rates. Two-sided alpha of 5% will be used. Reliable improvement is defined as a reduction of > 5 points on PHQ-9 scores based on severity classifications pre-to-post treatment.

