**Methods:**

The study is being conducted in partnership with Barwon Health’s Mental Health, Drugs & Alcohol Service (Geelong, Victoria), from which 184 participants from its service and surrounding regions are being recruited. Eligible participants with elevated psychological distress are being randomised to CALM or psychotherapy. Each takes a trans-diagnostic approach, and comprises four weekly (weeks 1-4) and two fortnightly (weeks 6 and 8) 90-min, group-based sessions delivered via Zoom (digital video conferencing platform). CALM focuses on enhancing knowledge, behavioural skills and support for improving dietary and physical activity behaviours, delivered by an Accredited Exercise Physiologist and Accredited Practising Dietitian. Psychotherapy uses cognitive behavioural therapy (CBT) delivered by a Psychologist or Clinical Psychologist, and Provisional Psychologist. Data collection occurs at baseline and 8 weeks. The primary outcome is depressive symptoms (assessed via the Patient Health Questionnaire-9) at 8 weeks. Societal and healthcare costs will be estimated to determine the cost-effectiveness of the CALM program. A process evaluation will determine its reach, adoption, implementation and maintenance.

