### Study aims

The primary aim is to examine the effectiveness of the CALM program for reducing depressive symptoms compared to a standard psychotherapy program. The primary outcome will be change in depressive symptoms at 8 weeks as measured by the Patient Health Questionnaire-9 (PHQ-9) [27]. Secondary aims include: (i) examination of the efficacy of CALM versus psychotherapy on other health outcomes (anxiety symptoms, psychological distress, health behaviours, health functioning and cardiovascular disease biomarkers), (ii) investigation of the cost-effectiveness of the CALM program relative to psychotherapy from healthcare and societal perspectives, and (iii) a process evaluation by which to determine the reach, adoption, implementation and maintenance (RE-AIM) [28] of the CALM program beyond the research period.

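### The primary outcome is worded both as change in PHQ-9 and as the 8-week score, and the analysis fixes neither the response nor the use of baseline; adjusting for baseline PHQ-9 would settle this at no cost

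*Protocol article*

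**What the plan says.** All references are to the protocol article.

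- **Study aims:** "The primary outcome will be change in depressive symptoms at 8 weeks", measured by the PHQ-9.
- **Abstract, Methods paragraph:** "The primary outcome is depressive symptoms (assessed via the Patient Health Questionnaire-9) at 8 weeks". The hypothesis, in the abstract's Background paragraph and at the end of the main Background section, is likewise about depressive symptoms at 8 weeks; the latter names PHQ-9 scores.
- **Data analyses:** "To compare continuous outcomes on the PHQ-9 in the primary analysis, between-group mean difference and confidence intervals (CIs) will be estimated" by GEE, with a sandwich variance for clustering. The sentence does not say whether the response is the 8-week score, the change or both time points, and it names no covariate.
- **Sample size:** the upper confidence limit for the "between-group mean difference on the PHQ-9 will be no larger than 2". The inputs are given as "Assuming a standard deviation of 4, one-sided type I error = 0.025 and 80% power". The SD is not tied to level, change or a baseline-adjusted residual.
- **Study design and Data collection:** participants are assessed before randomisation, and the questionnaire battery is given at baseline and at 8 weeks. Data analyses already uses the pre-treatment PHQ-9 for its exploratory remission and recovery outcomes.

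**The concern.** Two definitions of the primary outcome stand side by side, and the analysis sentence does not choose between them. An analysis plan that adopts either one will disagree with part of the published article.

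The choice matters in a non-inferiority trial with a 2-point margin. Unadjusted, level and change give different point estimates and confidence intervals from the same data. If the choice stays open until the data are seen, it is a freedom that could decide a result near the margin. The power statement also has no fixed meaning until the SD is attached to one of the quantities.

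**Working it through.** **Inputs from the article.** Margin 2, SD 4, one-sided alpha 0.025, power 80%, 80 per arm before attrition (all Sample size). Data analyses repeats the alpha: "One-sided type I error of 0.025 will be used for all non-inferiority analyses". Sample size also contains "one-sided alpha of 5% was used for non-inferiority margin", which conflicts with this; that is a separate point, and 0.025 is used here.

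**Assumed.** The correlation r between baseline and 8-week PHQ-9 is not given, so 0.3 to 0.7 is shown. Baseline and 8-week SDs are taken as equal. The true difference is 0 and clustering is ignored.

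**1. The plan's own figure.** n per arm = 2 × [4 × (1.96 + 0.8416) / 2]² = 62.8, so 63 per arm and 126 in total. The article says "a total sample size of *N* = 160 (*n* = 80 participants assigned to each group) will be required". The stated inputs do not reproduce 160; this too is a separate point. The article's 80 per arm is used below.

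**2. Power if 4 is the SD of the 8-week score.** Power = Φ(2 / (SD × √(2/80)) − 1.96), with
- level: SD = 4
- unadjusted change: SD = 4 × √(2(1 − r))
- baseline-adjusted: SD = 4 × √(1 − r²)

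For level, the standard error is 4 × √(2/80) = 0.632 and power is Φ(3.162 − 1.96) = 88.5%.

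| r | Level | Change | Adjusted | 95% CI half-width: level / change / adjusted |
|---|---|---|---|---|
| 0.3 | 88.5% | 76.2% | 91.2% | 1.24 / 1.47 / 1.18 |
| 0.4 | 88.5% | 82.3% | 93.2% | 1.24 / 1.36 / 1.14 |
| 0.5 | 88.5% | 88.5% | 95.5% | 1.24 / 1.24 / 1.07 |
| 0.6 | 88.5% | 94.2% | 97.7% | 1.24 / 1.11 / 0.99 |
| 0.7 | 88.5% | 98.3% | 99.3% | 1.24 / 0.96 / 0.89 |

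The adjusted variance is (1 − r²) times that of level and (1 + r)/2 times that of change. In large samples it is therefore never the larger, whatever r is.

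**3. Power if 4 is instead the SD of change.** The level SD is then 4 / √(2(1 − r)), which is 3.38 at r = 0.3 and 5.16 at r = 0.7. Unadjusted power for level runs from 96.3% down to 68.8%.

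**4. How far the estimates can part.** With complete data and simple arm means, change difference = level difference − baseline difference. Suppose CALM starts 1 point lower and the 8-week difference is 0.3. The change estimate is 0.3 + 1 = 1.3. At r = 0.5 both half-widths are 1.24, so the upper limits are 1.54 (below 2) and 2.54 (above 2). The adjusted estimate is 0.3 + 0.5 × 1 = 0.8, with an upper limit of about 0.8 + 1.07 = 1.87.

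**5. Why adjustment removes the ambiguity.** If Y = a + τT + βB, then Y − B = a + τT + (β − 1)B. The residuals are the same, so τ and its standard error are the same. In one simulated data set (160 people, 20 groups, GEE with sandwich variance) the adjusted model gave −0.067 (SE 0.460) for both responses. The unadjusted models gave −0.186 for level and 0.033 for change.

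**The case against.** A reader might infer that the plan specifies an unadjusted comparison. It does not. The article never uses that word, and GEE can carry baseline as a covariate or as a repeated response. Covariates are commonly left to the full protocol or analysis plan, neither of which is shown, so their absence from a condensed article is not an error. This objection stands. What remains is the contradictory wording of the outcome, which the analysis sentence leaves unresolved.

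A reader might also infer that allocating in small batches makes baseline imbalance likely. Imbalance in the overall mean depends essentially on the numbers per arm, and randomising within batches does not increase it. With an assumed baseline SD of 4 and 80 per arm, the standard error of the baseline difference is 0.632. A 1-point imbalance is then 1/0.632 = 1.58 standard errors, about an 11% chance counting both directions. The example in step 4 is possible, not expected, and it changes the conclusion only for a result near the margin.

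Nor do the documents show that the 8-week score is under-powered. On the stated SD and 80 per arm, its power is 88.5% before clustering if 4 is the SD of that score.

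Finally, level and change have the same expected treatment effect under randomisation, so the margin applies to one target under either wording. That is correct and limits the seriousness. It does not make the realised estimates, their precision or the meaning of the SD the same.

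**Conclusion.** The concern holds as a contradiction in how the primary outcome is worded, joined to an analysis sentence and an SD that do not resolve it. It does not show that a wrong analysis is planned.

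With 4 as the 8-week SD, 80 per arm, no clustering and r from 0.3 to 0.7, power is 88.5% for level, 76% to 98% for unadjusted change and 91% to 99% with adjustment. The variance reduction against level is r²: 9% at r = 0.3, 25% at 0.5 and 49% at 0.7. These sizes rest on an assumed r and on equal SDs. Clustering would lower all the powers. It would also dilute the relative gain somewhat, because baseline does not explain variance that arises in the therapy groups after randomisation. In large samples the ordering, with adjustment never worse than either alternative, does not depend on the value of r.

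Baseline adjustment is therefore a free improvement that also makes the choice between level and change irrelevant to the treatment estimate.

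**What to change.** - Define the primary endpoint as the PHQ-9 score at 8 weeks, and reword Study aims to agree with the abstract and the hypothesis.
- In Data analyses, state that the CALM minus psychotherapy difference comes from the clustered GEE with the 8-week score as response and baseline PHQ-9 as a covariate, and that its confidence interval is the one compared with the margin of 2.
- In Sample size, state whether the SD of 4 is that of the 8-week score, of change or of the baseline-adjusted residual.

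The cost is wording in the protocol and analysis plan, settled before outcomes are compared by arm. No new data, visits or participants are needed.

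### The protocol fixes a Huber sandwich variance for the primary CI but states no small-sample correction or t reference, although its figures imply only about 18 to 37 therapy groups

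*Protocol article*

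**What the plan says.** Under Study design, the protocol article describes a two-arm "individually randomised group treatment (IRGT), non-inferiority trial" with 1:1 allocation and 184 participants. Under Recruitment and informed consent, baseline visits are booked once enough people have enrolled "to form groups (minimum 5, maximum 10, per group").

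Under Sample size, non-inferiority requires that the upper confidence limit of the "of between-group mean difference on the PHQ-9 will be no larger than 2". The planning inputs there are SD 4, one-sided error 0.025 and 80% power, giving 160 participants, raised by 15% to 184.

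Under Data analyses, the mean difference and its CI are to be "estimated using generalised estimating equation techniques, with Huber Sandwich Estimator of variance to account for clustering", and "One-sided type I error of 0.025 will be used for all non-inferiority analyses".

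The article does not give the number of therapy groups, the cluster unit, the working correlation, the reference distribution, or any finite-sample adjustment of the variance.

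**The concern.** The classical sandwich variance is justified when the number of clusters is large. With few clusters it is biased downwards, because the residuals from which it is built have been shrunk by fitting the means. A normal quantile also ignores the sampling error of the variance estimate. Both faults make the CI too short.

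In a superiority trial that means too many false positives. Here it acts on the upper limit that is compared with 2, so the lifestyle program would be declared non-inferior more often than the declared 2.5% when it is in truth worse by the full margin. The method is named and so is the error rate. The question is whether the first delivers the second at the group sizes that the protocol sets.

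**Working it through.** **Inputs from the protocol article.** N = 184 and margin 2, SD 4 (Sample size); groups of 5 to 10 (Recruitment and informed consent); 1:1 allocation (Study design); one-sided 0.025 (Data analyses, and the planning inputs under Sample size).

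**The plan's own figures.** 160 × 1.15 = 184, as stated. The 160 itself does not follow from the stated inputs: 2 × (1.960 + 0.842)² × 4² / 2² = 62.8, so 63 per arm or 126 in total. That is a separate point, and nothing below depends on it.

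**Number of groups.** 184/10 = 18.4 and 184/5 = 36.8, so about 18 to 37 in total, or 9 to 18 per arm.

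**Exact error for equal group sizes.** Let k be the groups per arm and K = 2k.
- The estimate is the difference between the two arms' averages of group means.
- The plain sandwich divides each arm's sum of squared deviations of group means by k² rather than by k(k − 1). It is therefore (k − 1)/k times the unbiased variance.
- At a true difference of 2, non-inferiority is falsely declared when the estimate plus q × SE falls below 2. The probability is P(t on K − 2 df > q × √((k − 1)/k)), where q is the quantile used for the CI.
- The CI width relative to the correct t-based CI, with q = 1.96, is 1.96 × √((k − 1)/k) / t(0.975, K − 2).

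Example for K = 18: √(8/9) = 0.9428, and 1.96 × 0.9428 = 1.848. P(t on 16 df > 1.848) = 0.0416. The width ratio is 1.848/2.120 = 0.872.

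| Groups (K) | 1.96 × √((k − 1)/k) | One-sided error, plain sandwich, 1.96 | Two-sided coverage | CI width ratio | One-sided error, plain sandwich, t(K − 1) |
|---|---|---|---|---|---|
| 18 | 1.848 | 4.2% | 91.7% | 0.872 | 3.2% |
| 24 | 1.877 | 3.7% | 92.6% | 0.905 | 3.0% |
| 36 | 1.905 | 3.3% | 93.5% | 0.937 | 2.8% |

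The CI is thus 12.8%, 9.5% and 6.3% too narrow. Scaling the variance by K/(K − 1) while keeping 1.96 still gives 3.8% at 18 groups and 3.1% at 36.

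**Simulation at a true difference of 2.** 40,000 runs per setting; attrition 13%, from 1 − 160/184; ICC is not given in the protocol, so 0 to 0.10 was assumed.
- Plain sandwich with 1.96: 4.1–4.4% (18 groups of 10), 3.7–4.0% (24 groups of 5–10), 3.2–3.3% (36 groups of 5). The ICC makes little difference.
- Kauermann-Carroll type correction with t(K − 2): 2.4–2.6% in all settings.
- Mancl-DeRouen type correction with t(K − 2): 1.9–2.2%, slightly conservative.

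**Exchangeable GEE with baseline adjustment** (2,000 runs per setting, ICC 0 and 0.05). Robust SE with 1.96: 5.2% and 3.9% at 18 groups; 3.4% and 3.3% at 36. Bias-reduced variance with t(K − 2): 2.0–2.7%. The Monte Carlo standard error at a rate of 4% is √(0.04 × 0.96/2000) = 0.4 points, so these agree with the exact results but are less precise.

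**The case against.** A reader might infer that the trial has chosen an uncorrected variance with 1.96. The article does not say so. It names the estimator and stops, and both features are inferred from silence. Only a condensed article is at hand. A finite-sample correction and a df rule are details that an analysis plan may well contain, and the corrected estimators are versions of the same sandwich, so adopting one contradicts nothing in the article. The references attached to the clustering adjustment might also describe a correction; they are not available here.

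The size depends on those open details. By the same formula, K/(K − 1) scaling with t(K − 1) gives 2.9%, 2.8% and 2.7% at 18, 24 and 36 groups, and K/(K − 2) scaling with t(K − 2) gives 2.5% throughout. The 4.2% end also needs nearly every group to be filled to 10, and the article gives no mean group size.

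All of this stands, and it limits the point to a conditional one. It does not remove it. The article does more than leave the variance to a later document: it names the classical estimator beside a declared error of 0.025. Read as written, that pair does not match at any group count that the protocol allows, and two simple partial repairs (K/(K − 1) scaling with 1.96, or t(K − 1) alone) do not close the gap.

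The unnamed cluster unit is no rescue either. If the participant were the cluster, the sandwich would not cover therapy-group clustering at all. In the same simulation, an interval that ignored the groups had one-sided error of 4.8% (18 groups) and 3.5% (36 groups) at an assumed ICC of 0.05.

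**Conclusion.** The point holds in conditional form. Used as named, with the therapy group as cluster and a normal quantile, the primary analysis has a one-sided false non-inferiority rate of about 3.3% (36 groups) to 4.2% (18 groups) against 2.5%, and a CI about 6% to 13% too narrow. With t(K − 1) alone the rate is still about 2.8% to 3.2%. The inflation is modest, but it favours a false claim. The change should be made; it is not a fatal flaw.

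The result rests on group counts derived from N and the group-size limits, on therapy group as the cluster, and on no shared batch variance. Both arms are filled from the same batches, so effects common to a batch could offset part of the inflation; the protocol gives no figure for this. The result hardly depends on the ICC. The benchmark is 0.025, which the Data analyses section and the planning inputs both give. The Sample size section also says that a "one-sided alpha of 5% was used for non-inferiority margin", which is a separate inconsistency.

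The documents do not support the stronger statement that the reported CI will be invalid.

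**What to change.** State in the analysis plan, before unblinding, that the cluster is the therapy group and that the primary CI uses a small-sample corrected sandwich (for example Kauermann-Carroll or Fay-Graubard) with a t quantile on about (number of groups − 2) df. Name both parts, because either one alone leaves some inflation. The estimand, margin and data collection do not change.

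A linear mixed model with a random therapy-group effect and Kenward-Roger df is an alternative. It is not an equivalent, since it replaces the robust variance with a model-based one and relies on the random-effects structure.

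The cost is a line of wording and a wider CI: 1/0.937 = 1.07 to 1/0.872 = 1.15, so about 7% to 15%, with some loss of power. If the analysis plan already specifies such a correction, it is enough to confirm that.
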